## **ETHICAL CONSIDERATIONS**

The study will be conducted in accordance with the International Conference on Harmonization (ICH) Guideline for Good Clinical Practice (GCP) all applicable subject privacy requirements and the guiding principles of the Declaration of Helsinki. Conduct of the study includes, but is not limited to, the following:

- Institutional Review Board (IRB)/Independent Ethics Committee (IEC) review and favorable opinion/approval of study protocol and any subsequent amendments.
- Subject/subject's parent(s) informed consent and subject informed assent, as appropriate.
- Investigator reporting requirements as stated in the protocol.

Freely given and written informed consent must be obtained from each subject and/or each subject's parent(s) and subject informed assent, as appropriate, prior to participation in the study. Those subjects who can only be enrolled in the study with the consent of the subject's LAR (legally acceptable representative) (e.g. minors), should be informed about the study to the extent compatible with the subject's understanding and, if capable, the subject should sign and personally date a written informed assent. It is required that the assent be signed by each

subject, if capable, in addition to the informed consent that is to be signed by his/her legal representative. It should be assessed whether an assent is required depending of the age of the study population and the local requirements.

The study protocol, questionnaires, and consents, will be reviewed and approved by the appropriate REB.

## **INFORMED CONSENT PROCESS:**

Informed consent will be sought from participants themselves or their parent/legal guardian on behalf of their child. Children who do not have the capacity to consent for themselves will sign an assent form in addition to their signed parental consent.

In order to ensure participant's rights are protected, those who sign an assent form will be flagged and their capacity to consent will be assessed annually at regular clinic visits. When a participant is deemed to have the capacity to consent for research study, a study team member will approach the patient to obtain their consent on their continued participation in the long-term storage of their biosamples for the study. The participant will be given a detailed explanation of the reason of re-approaching them for consent and all questions will be answered to their satisfaction. Participants will be given a choice if they would like to continue participating in the study by allowing long-term storage of their collected biosamples, or if they would like to withdraw their samples from the study.

Participants will be asked to sign the consent form to indicate their preferences of continued participation and will be given a copy of their signed consent form for their records. Participants who would like to withdraw their samples will be noted, and samples will be withdrawn from the biobank.

Study will be kept open for up to 15 years post study closure (data collection ended) to ensure all participants who acquired capacity to consent for themselves are approached.

## **Risks and Benefits:**

**Potential Risks:** Blood samples are collected as part of standard of care pre and post-transplant. We will be collecting the data obtained from the tests performed.

**Potential Benefits:** There may or may not be direct benefit to participants. We anticipate that the information learned from this study will benefit other children on HDF type of dialysis.

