#### **Inclusion criteria:**

- Incident or prevalent HD patients
- Under 18 years old

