## **SAMPLES:**

### **Blood sampling:**

- At baseline and 3 months (= end of study)
- 18 ml blood; to be collected from the patient's vascular access just before they start dialysis. Please collect the sample on a mid-week session of dialysis.
- Please collect using the 3H study packs provided.
- Centrifuge and save serum in 10 bottles and store at -80 degrees
- Courier to the central laboratory in Heidelberg (exactly the same as for 3H samples)

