### **TIME-LINE:**

Baseline – At the time of study entry when the first blood samples for the study are collected. This is the same as the bloods for the 3H study.

End of study (3 months of the new dialysis modality) - Assessment will be done at the end of 3 months of HDF

[figure not shown]

[figure not shown]

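### The protocol's only risk statement describes standard-of-care transplant sampling, but the study takes 18 ml of study blood at two time points from children on dialysis

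*Protocol*

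**What the plan says.** The whole of the Potential Risks text in the protocol (Informed Consent Process, Risks and Benefits) is two sentences: "Blood samples are collected as part of standard of care pre and post-transplant" and "We will be collecting the data obtained from the tests performed". No other risk statement appears in the protocol as shown.

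The Samples section, under Blood sampling, gives a different account. Its instruction is "18 ml blood; to be collected from the patient's vascular access just before they start dialysis", at baseline and again at 3 months, on a mid-week session, and "Please collect using the 3H study packs provided". The serum is divided into 10 bottles, frozen at -80 degrees and couriered to a central laboratory. The Time-Line adds, of the baseline blood, "This is the same as the bloods for the 3H study". Specimen Handling & Storage provides for leftover sample to be kept for other research unless the participant refuses.

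On who is studied, the inclusion criteria name incident or prevalent haemodialysis patients and set one age limit, "Under 18 years old". The exclusion criteria mention neither age nor weight. Identifying Potential Study Subjects draws participants from children enrolled in HDF-3H.

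**The concern.** The risk statement and the sampling instructions cannot both describe this study. Read alone, the risk statement places the study in transplantation and presents the blood as routine care whose results are merely collected. The sampling instructions describe blood drawn for study purposes from children on dialysis.

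The mismatch is more than a slip of wording. Ethical Considerations sends the protocol and consents to an ethics board and requires consent or assent, and all participants are minors. The risk section is where the burden on them should be stated. Here it omits the research blood draw, the one physical procedure that the protocol specifies for research purposes. What is at stake is participant protection and a sound basis for approval. No endpoint, comparison or analysis is affected.

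**Working it through.** The protocol states no figure for blood burden, so there is none to reproduce. The check is mainly a comparison of texts.

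**1. Setting.** The risk text refers to blood taken before and after transplant. The Study Abstract, the inclusion criteria and Identifying Potential Study Subjects all describe children on haemodialysis or haemodiafiltration. Transplant is not a study event anywhere else in the protocol.

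**2. Source of the blood.** The risk text says standard of care. Blood sampling specifies a set volume, study packs, frozen serum and a courier to a central laboratory.

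**3. Could the 18 ml be the routine sample?** No. Case Report Forms and Source Documents has routine results (blood count, urea, creatinine, electrolytes, ferritin, PTH and others) recorded from patients' files. The List of Markers covers oxidised LDL, nitrotyrosine, interleukins, ADMA, microparticles and similar assays. PTH is on both lists, and CRP, which is checked on the assessment day, recurs as hsCRP. The remaining markers are not among the routine tests.

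**4. Which draws belong to SWITCH?** The Time-Line says that the baseline blood is the HDF-3H blood. It says no such thing of the 3-month blood. Blood sampling does not say that 18 ml applies to each time point, but that is the natural reading. On that reading:

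- total over the study: 2 × 18 ml = 36 ml
- added by SWITCH if only the baseline draw is shared: 36 − 18 = 18 ml

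**5. Scale by body size.** The protocol gives no body weights or blood volumes, so both are assumptions. The formula is: share of blood volume = 18 ml ÷ (weight × blood volume per kg).

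| Assumed weight | ml/kg per draw | at 80 ml/kg | at 70 ml/kg |
|---|---|---|---|
| 40 kg | 18/40 = 0.45 | 18/3200 = 0.6% | 18/2800 = 0.6% |
| 20 kg | 18/20 = 0.9 | 18/1600 = 1.1% | 18/1400 = 1.3% |
| 10 kg | 18/10 = 1.8 | 18/800 = 2.3% | 18/700 = 2.6% |

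Because the volume is fixed, the burden per kg at 10 kg is four times that at 40 kg (1.8 ÷ 0.45 = 4), whatever blood volume is assumed.

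**The case against.** The best defence is that SWITCH is a sub-study. Its baseline blood and baseline data come from HDF-3H, the packs and handling are those of HDF-3H, and the risk text may mean only that SWITCH uses results obtained elsewhere. Part of this stands, since the blood that SWITCH itself adds may be a single draw. It does not rescue the risk text. HDF-3H blood is also study blood, and nothing connects it with transplant.

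Several stronger readings are tempting, and the documents do not support them:

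- **That the risk text excludes any research sampling.** It does not say that standard-of-care results are the only ones used. The contradiction lies in what it describes and what it leaves out.
- **That SWITCH takes 36 ml of additional blood.** The Time-Line rules this out for the baseline draw. Whether the 3-month draw is also an HDF-3H draw cannot be seen.
- **That very small infants will be enrolled.** This protocol lists no lower age or weight limit, but participants come through HDF-3H, whose limits are not shown. At an assumed 5 kg one draw would be 3.6 ml/kg, but no document shows that such a child would enter.
- **That the volume is excessive.** The documents give no limit to compare it with. The blood comes from the vascular access just before dialysis, so no separate needle puncture is implied.
- **That the ethics board and families are misled.** The board reviews the whole protocol, including the 18 ml. The consent pages were removed before this review, so what families are told is unknown.
- **That markers will be lost selectively in small children.** Nothing says that sites will refuse or under-fill draws, and rules for short samples may sit in laboratory instructions not shown here.

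**Conclusion.** The risk statement is wrong as written and must be corrected. It attributes the blood to routine transplant care, while the protocol's own instructions call for 18 ml of study blood at two time points from children on dialysis, with the baseline draw shared with HDF-3H. This conclusion rests on the text alone and needs no assumption.

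The size of the omitted burden is less certain. It is 18 ml per draw if the volume applies at each time point. Under assumed weights and 80 ml/kg, that is about 0.6% of blood volume at 40 kg and 2.3% at 10 kg. These figures show why a committee should see the fixed volume stated. They do not show harm, and they do not justify requiring a weight cap or an order for dropping markers.

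**What to change.** Reconcile Risks and Benefits with Blood sampling and the Time-Line. Replace the transplant sentences with a description of the draws actually made:

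- the volume, and whether it applies at each time point;
- the two time points, and the sampling from the vascular access before dialysis;
- which draw or draws are shared with HDF-3H;
- the research purpose and possible storage;
- the risk of the draws.

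State that the volume does not vary with body size, and give or cite any age or weight limit inherited from HDF-3H, so that the ethics committee can judge the volume in small children. Check that the consent and assent text agrees.

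The cost is a wording amendment and its ethics review. Sampling, markers and analysis do not change.

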## **HEALTH-RELATED QUALITY OF LIFE QUESTIONNAIRE (BASELINE AND 6-MONTHLY INTERVALS):**

Three information and screening questionnaires will be given to children and their parents: Pi-ED will screen for emotional distress (depression and anxiety), PedsQL for health impacts on QoL and SDQ for emotional well being and pro-social relationships. In addition, we will acquire information on post-dialysis recovery time, school and college attendance and sleep pattern.

1. PedsQl (Paediatric Quality of Life)
2. SDQ (Strengths, Difficulties Questionnaire)
3. Pi-Ed (Paediatric Index of Emotional Distress)

### **Quality of life (QoL) questionnaires:**

Three validated questionnaires:

PedsQL (Pediatric Quality of Life)

SDQ (Strengths-Difficulties Questionnaire)

Pi-ED (Paediatric Index of Emotional Distress) will be used.

### **Case Report Forms and Source Documents:**

All data will initially be collected on paper CRF's at each site. The site investigator must retain a copy of the CRF and changes in the study files. Subject data necessary for analysis and reporting will then be entered/ transmitted into a validated database or data system. All data will be entered in the HDF-3H Registry (<http://pedpd.org/index.php>) only – no separate data entry required. Clinical data management will be performed in accordance with applicable International Child Health standards.

Data required (all part of the HDF-3H study)

(note, all baseline data will be available from HDF-3H)

- On the day of assesment rule/out any infection, inflammation with symptoms, physical examination ( including and examination of vascular access about hyperemia, purulent discharge) and laboratory ( leukocytosis, CRP, urine analysis - if patient is not anuric).
- Antropometric measurements ( dry weight, height)
- Type of vascular Access, dialysis modality, machine, Qb,Qd, replacement volume, dialyzer, dialysate will be recorded

- Kt/v, routine blood tests ( hemogram, urea, creatinin, uric acid, electrolytes, HCO3, lipids (optional), ferritine, PTH) , drugs will be recorded from patients' files

### **Records Retention:**

Hard copies of participant data records (source documents) will be retained on site and at the coordinating center for 7 years after the last study follow up is completed. Electronic data in the centralized research database will be retained for up to 20 years after the last study follow up is completed and analyses related to the principal research or ancillary studies has been completed. After this point, written copies of the research records will be destroyed.

Information retained (electronic and hard copy) that links the electronic database with individual participants will also be destroyed or deleted.

### **ORGANIZATION AND PARTICIPATING CENTERS:**

The study will be coordinated centrally. The coordinating center will include the multicenter research coordinator who will manage communication with sites. The site research nurse at the coordinating center will also provide oversight over standard operating procedures, and contribute to training site research associates/nurses. The core site coordinator and multicenter research coordinator will be accountable to the principal investigator.

Each center will have one designated site investigator who will be responsible for the conduct of the study at their site, and will employ a research nurse/associate to complete the site study visits. The site research associate will be responsible for completing study visit, collecting data at the visit and complete data collection for results that come after the visit, for sample collection, processing and storage.

### **Data Monitoring Committee:**

A Data Monitoring Committee will oversee the study and interim analysis.

### **DATA STORAGE:**

#### **Confidentiality and Security**

The study will be conducted in accordance with the ethical principles of the Declaration of Helsinki and will be consistent with Good Clinical Practices (GCP) and applicable regulatory requirements under PHIA . Each site will take appropriate measures to ensure the confidentiality of the data and the well-being of their participants. Information gathered in this research study may be published or presented in public forums; however participant names and other identifying information will not be used or revealed. Organizations such as the local Research Ethics board may inspect and/or copy research records for quality assurance.

Individuals who will have access to records containing personal health information such as hospital medical records will be restricted to the investigators of the study and study personnel associated with the trial.

Participants in the study are assigned a unique study identification number that is linked at the site only. This identification number is the only patient identifier stored with the research data. The participant is not tracked through the study by name, social security number, medical record number, or other distinct personal identifiers. A log of the participant names and participant ID numbers as well a sample code and participant ID will be maintained in a locked area at each clinical site. The participant and sample log will remain at the site of origin. Any communication between the coordinating centers and individual sites will occur via the participant or sample ID number. Any forms or documents sent to the clinical coordinating centers, IRB or Regulatory Authorities will have all personal identifying information removed, and replaced with the participant ID number. All research reports, articles, and presentations will report only aggregate findings.

The hardware will reside within a restricted access area managed by the Computer Operations group and site administrators will have remote access to the servers. Access to the content or to any components of the database will require login authentication (i.e., username and password). The privacy of the participant content is ensured and managed by the database manager. Connection to the site will be over HTTPS (secured socket layer) and therefore all data entered will be encrypted and trusted.

The electronic database will not contain personal health or otherwise identifying information. The database will be permanently de-linked from identifying information after site linking data has been deleted. Thereafter, stored data may be used for supplementary analyses as anonymized data. At this point, it will no longer be possible to collect or include additional patient-specific information.

## **SAMPLES:**

### **Blood sampling:**

- At baseline and 3 months (= end of study)
- 18 ml blood; to be collected from the patient's vascular access just before they start dialysis. Please collect the sample on a mid-week session of dialysis.
- Please collect using the 3H study packs provided.
- Centrifuge and save serum in 10 bottles and store at -80 degrees
- Courier to the central laboratory in Heidelberg (exactly the same as for 3H samples)

### **Specimen Handling & Storage**

As part of the main study, blood samples are stored for testing. We may not use the entire sample collected in this research study. We will keep the sample, for possible use in other research. Future research studies may be performed by the study collaborators, the research team doing this study and our research staff, involved in kidney disease research. The Investigator at the coordinating centre will take responsibility for sending samples to researchers who work with this team.

Participants can refuse Consent for use of blood samples in future research, but still consent to the proposed study. If participants refuse to have their blood stored for future research their blood samples will be destroyed at the end of this study.

The stored samples will be labeled by study number only with no identifying information. After the study is complete the samples that are stored will be linked to study data using a unique identifier but not to participant's identity. Only the Investigator at participating sites and his/her research staff will have access to the participants' identifying information which will be kept in a locked research space at this centre. Any identifying information on paper or stored on a computer (password protected) will be in a locked office and will be accessed only by research staff at this site. We will not be able to give out any information that identifies the participant, to the scientists who receive the samples.

At any time participants may ask to stop allowing the storage of their samples. If a decision is made to stop allowing the use of stored samples, they will be destroyed. Information and results already collected up to that time will be kept in the study information files.

Please see the "Governance of Biospecimen" attached.

### **TIME-LINE:**

Baseline – At the time of study entry when the first blood samples for the study are collected. This is the same as the bloods for the 3H study.

End of study (3 months of the new dialysis modality) - Assessment will be done at the end of 3 months of HDF

[figure not shown]

[figure not shown]

**Time "0"**

**Blood  
sampling**

**IPHN data  
entry registry**

**"Final"**

**Blood  
sampling**

**IPHN data  
entry registry**

## **LIST OF MARKERS**

### **OXIDATIVE STRESS:**

#### **LIPIDS:**

- Oxidized LDL
- Lipid hidroperoxide

#### **PROTEINS:**

- Nitrotyrosine

#### **ANTIOXIDANTS:**

- Gluthatione peroxidase
- SOD

#### **INFLAMMATORY MARKERS:**

- LP-PLA2
  - Pentraxin 3
  - IL 6
  - IL 10
  - TNF alpha
  - hsCRP
- 
- ADMA
  - AGEs
  - B2 microglobulin
  - PTH

### **ENDOTHELIAL MARKERS**

1. Nitric oxide
2. ADMA and SDMA

3. oxLDL
4. Endothelial ROS production
5. Microparticles (endothelial, platelet, leukocyte)
6. iCAM and VCAM
7. HDL function (including NO production) in a sub-group

